#### Exploratory Analyses

As part of the primary investigator’s precision health initiative, we aim to include predictive modeling of the intervention. Traditionally, trials contrast the mean difference between two groups, but do not address individual variability. Intuitively, we know that some individuals will respond well to an intervention, others might not, and some might further be harmed by it. We aim to predict how individuals will respond to an intervention using only individual baseline characteristics. Therefore, we will measure characteristics at baseline related to the behavior-change theory, in particular, importance and self-efficacy, as well as conventional baseline characteristics (age, gender, etc). These characteristics will then be used to inform statistical models that predict individual outcomes.

Predictive analysis requires a radically different approach of assessing a model’s performance, as explaining and predicting are two different tasks [43]. We will use a Bayesian approach using shrinkage priors [44,45], which allows us to include all characteristics measured at baseline and learn which ones should be included in the predictive model from the data. The result is a model that can tell individuals how likely it is that the intervention has a positive effect on them specifically, rather than quoting the group mean difference.

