### Design

To investigate the effect of the intervention, a randomized controlled trial (trial registration: ISRCTN33869008) will be conducted at 20 surgical departments in southeast Sweden. The trial will follow a two-arm single-blind parallel-group design. Figures 1 and 2 offer an overview of the design in the form of a SPIRIT (Standard Protocol Items: Recommendations for Interventional Trials) figure and CONSORT (Consolidated Standards of Reporting Trials) flowchart, respectively. The trial began in October 2018.

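### The exploratory model is said to give individuals their own probability of benefit, which a parallel-group trial only bounds; its output should be described as a predicted effect for a baseline profile

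*Protocol article*

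**What the plan says.** The point arises in the protocol article, Methods, Statistical Analysis, Exploratory Analyses. The motivation given there is that "some individuals will respond well to an intervention, others might not, and some might further be harmed by it". The aim follows: "We aim to predict how individuals will respond to an intervention using only individual baseline characteristics". On the method, the article says "These characteristics will then be used to inform statistical models that predict individual outcomes" and "We will use a Bayesian approach using shrinkage priors". It then names the deliverable: "The result is a model that can tell individuals how likely it is that the intervention has a positive effect on them specifically", and sets this against the usual summary with the words "rather than quoting the group mean difference".

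The Design section says: "The trial will follow a two-arm single-blind parallel-group design". Each participant's outcome is therefore recorded under one allocation and never under the other.

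The Exploratory Analyses section does not say which outcome is modelled. I assume one of the two binary primary outcomes defined under Measures (prolonged abstinence or point prevalence of abstinence).

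**The concern.** Randomisation identifies how often people with given baseline characteristics abstain with the intervention, and how often similar people abstain without it. The difference is an average effect for that profile. Whether the intervention has a positive effect on one particular person is a different matter. That depends on what the same person would have done under both allocations, and nobody is observed under both. Shrinkage priors help to decide which covariates matter, but they carry no information about how the two outcomes go together within a person. Adding covariates does not remove the gap either, unless the predicted risks approach 0 or 1.

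What is at stake is interpretation. The natural output of a Bayesian model is a posterior probability that an effect exceeds zero. If that figure is given to someone as the chance that the programme will work for them, certainty about an average is presented as a personal chance of benefit. The article names individuals as the audience, and they are poorly placed to notice the substitution.

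**Working it through.** **Inputs.** The article gives no figure for the exploratory model, so there is none to reproduce. I use the planning rates from the Power Calculation section: p1 = 0.259 (intervention) and p0 = 0.146 (control). As a check that these rates underlie the plan, the standardised difference is 0.113 / √[(0.259 × 0.741 + 0.146 × 0.854)/2] = 0.113 / 0.398 = 0.284, which rounds to the stated Cohen d of 0.3.

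**Step 1: what the two arms leave open.** Let Y1 and Y0 be a person's abstinence (1 = abstinent) with and without the intervention, and let b = P(Y1 = 1 and Y0 = 1), the share who would abstain either way. Then

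- P(benefit) = P(Y1 = 1, Y0 = 0) = p1 − b
- P(harm) = P(Y1 = 0, Y0 = 1) = p0 − b

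The trial estimates p1 and p0. It gives no information on b beyond max(0, p1 + p0 − 1) ≤ b ≤ min(p1, p0). Here 0.259 + 0.146 − 1 is negative, so 0 ≤ b ≤ 0.146.

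**Step 2: bounds at the planning rates.**

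- Benefit: from 0.259 − 0.146 = 0.113 to 0.259 − 0 = 0.259
- Harm: from 0.146 − 0.146 = 0 to 0.146 − 0 = 0.146

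**Step 3: three populations that would produce the same trial data.**

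| Assumption | b | Benefit | Harm | Abstinent under neither |
|---|---|---|---|---|
| Nobody harmed | 0.146 | 0.113 | 0 | 0.741 |
| Y1 and Y0 independent | 0.259 × 0.146 = 0.038 | 0.221 | 0.108 | 0.633 |
| No one abstinent under both | 0 | 0.259 | 0.146 | 0.595 |

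In every row benefit + b = 0.259 and harm + b = 0.146, so the arms look identical. Only the first row gives a single value that the data supply (benefit equals the risk difference). It requires that nobody is harmed, whereas the section itself says "others might not, and some might further be harmed by it".

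**Step 4: the posterior probability is a different quantity.** With the planned 192 per group and these observed rates, the standard error of the difference is √[(0.259 × 0.741 + 0.146 × 0.854)/192] = 0.0406, and z = 0.113 / 0.0406 = 2.78. Under a flat prior and a normal approximation, the posterior probability that the average effect is positive is about 0.997. Over the same population, the share who benefit is between 0.113 and 0.259. Both statements are correct together, because they answer different questions.

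**Step 5: within a profile.** The formulas in Step 1 hold for any baseline profile, with that profile's own p1 and p0. The numerical bounds then differ. Averaged over profiles, they can be no wider than those in Step 2 and will generally be narrower.

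**The case against.** The strongest reply is that the planned analysis is sound and that the sentence has an identified reading. The models use baseline characteristics only, predict outcomes and are Bayesian. The likelihood of a positive effect can therefore be read as the posterior probability that the effect for someone with these characteristics exceeds zero, and the contrast with the group mean can be read as conditional versus marginal effect. The section never mentions joint potential outcomes. The harm remark is offered as intuition, not as an estimand. No output format or delivery tool is described, so the misreading is foreseeable rather than planned. The analysis is labelled exploratory.

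Most of this stands. A reader might infer that the model is invalid, or that whatever it reports will be wrong. The article does not support that: with randomised data the model validly estimates each profile's abstinence probability in each arm, their difference, and the posterior probability that this difference is positive. A reader might also take 25.9% as a ceiling on anyone's chance of benefit. It is a population figure from an earlier trial in university students, and a profile with a higher abstinence rate under the intervention has a higher ceiling. Likewise, the 0.997 in the working concerns the overall average effect; posteriors for single profiles would be less certain.

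What does not stand is that the sentence can be left alone. Its emphasis on the specific person, its contrast with the group mean and the preceding talk of responders and harmed individuals all favour the literal reading. Further detail in an analysis plan could redefine the output, but it could not make the literal statement true for this design.

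**Conclusion.** The concern holds as a fault in the stated output of an exploratory analysis. Taken literally, the deliverable is a personal probability of benefit, which the design only bounds. No identifying assumption is stated, and the text's own remark on harm conflicts with the usual one. At the planning rates the bounds are 11.3% to 25.9% for benefit and 0% to 14.6% for harm. These figures assume a binary outcome and the earlier trial's rates, and they illustrate the population, not any profile.

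The model, the primary outcomes, the tests and the sample size are unaffected. The change is nonetheless worth making, because following the sentence as written would present a profile-level quantity as a personal chance.

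**What to change.** Replace the sentence on the model's result, here and in any analysis plan or report that carries it forward, with wording along these lines: for people with a given baseline profile, the model reports the predicted probability of abstinence with the intervention, the predicted probability without it, and their difference, each with a credible interval. Any posterior probability of a positive effect refers to the average effect among people with that profile; it is not the chance that a particular individual will benefit.

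The fitted model and the data stay the same, and no additional participants are needed. The cost is a few lines of text, a different summary from the same posterior, and a less striking claim.

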### Power Calculation

A previous study that explored the effect of an SMS-based smoking-cessation intervention for Swedish university students found that 25.9% in the intervention group had not smoked more than 5 cigarettes in the past 8 weeks compared to 14.6% in the control group [16]. This is comparable to a Cohen *d* value of 0.3, which can be interpreted as a small-to-medium effect. In general, this is in line with what we should expect from brief digital lifestyle interventions. In order to identify a statistically significant difference between the two groups, under the expected Cohen *d* value of 0.3, we will need to recruit 192 patients per group (at 0.8 power and .05 significance level). Assuming a 10% loss to follow-up, the final sample size required is 434 patients.

With 20 surgical departments recruiting participants over 12 months, we would require each department to recruit an average of 1.8 participants each month. If necessary, the recruitment period of 30 months will require 0.7 recruited participants on an average per month per department. We believe that this is feasible, given the commitment from the departments.

## Results

At the time of submission of this protocol, recruitment had not yet started. Recruitment started in late October 2018 and is expected to last for a maximum of 30 months. The first results are expected to be available approximately 3 months after the final date of recruitment.

## Discussion

The project within which this trial is contained is focused on perioperative smoking cessation, mainly with a focus on reducing postoperative complications. However, more generally, smoking is responsible for approximately 9.6% of the total disease burden in Sweden, and the annual number of new younger smokers is between 16,000 and 20,000 [2,6]. Approximately 9% of the general population of Sweden comprises daily smokers [3]. Globally, smoking is the most important preventable cause of ill health and death, where for every death related to smoking, more than 20 additional individuals suffer from at least one serious smoking-related illness [1]. Thus, any opportunity presented to help individuals to quit smoking should be taken advantage of.

Surgical departments in Sweden are obligated to inform patients about complications related to smoking and surgery, but should also offer help to quit smoking. However, structural problems and scarcity of time and resources lead to patients simply being instructed to quit, and perhaps, referred to a primary health care clinic. Some surgical departments have staff dedicated to helping patients quit smoking, but not many departments can offer this resource. An SMS-based smoking-cessation aid can be effective in helping individuals quit smoking and is a very simple and time-efficient tool for surgical departments to use. Health care professionals only need to inform patients about a phone number, and patients can sign up by sending a single SMS message.

This trial will collect data on the effectiveness of the intervention and further the growing evidence on SMS-based interventions for smoking cessation. This will help decide whether the intervention should be made generally available for all surgical departments in Sweden. Furthermore, the participation of several departments in the trial will give us a unique opportunity to identify key barriers in current practice and adapt the sign-up procedure to reach as many patients as possible and disrupt current routines as little as possible. These insights will lay the foundation for future implementation of research projects. If the intervention is found to be effective, it might have a substantial impact on not only the number of postoperative complications but also the disease burden in Sweden caused by smoking, in general.

A limitation of this study is that is that it does not include cessation of smoke-free tobacco (such as snuff). To our knowledge, no studies have thus far identified an association between smoke-free tobacco and postoperative complications. Thus, the benefits of an intervention targeting smoke-free tobacco will have to be evaluated in a separate trial. Another limitation is the use of nonbiochemical verification at follow-up. However, the Society for Research on Nicotine and Tobacco recommends that in population-based studies with limited face-to-face contact, it is neither required nor desirable to use biochemical verification [39]. Finally, this trial has been designed to power the statistical analyses of two primary outcome measures; thus, analyses of secondary outcome measures and mediation measures should be regarded as preliminary and exploratory work.

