### Previous Research and Findings

Over the past few years, it has become more evident that short message service (SMS)–based interventions can help individuals quit smoking. In a Cochrane review from 2016 [14], it was indicated that long-term quit rates increased by 67% among those who were given access to SMS-based smoking-cessation interventions compared to those who were not. These findings were supported by a second meta-analysis conducted the same year, which found that abstinence increased by 63% with the use of SMS-based interventions [15].

Our research group has previously investigated the use of an SMS-based intervention (NEXit) for smoking cessation among university students in Sweden [16-18]. The intervention was evaluated using a two-arm, parallel-group randomized controlled trial including 1590 participants between the ages of 21 and 30 years. With respect to 8-week prolonged abstinence, a statistically significant difference was found between the intervention group (25.9%) and control group (14.6%). Differences in the 4-week point prevalence between the groups were also statistically significant (20.6% versus 14.2%). The intervention has now been adapted to a younger age group and is currently in trial among high-school students in Sweden [19].

There is, however, no research in Sweden or elsewhere on the use of SMS-based interventions for smoking cessation prior to surgery. Given the success of the approach in other contexts and the importance of smoking cessation prior to surgery, it is valuable to determine if such an approach could work in this context.

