#### Measures

All questions asked at baseline and subsequent follow-ups can be found in Multimedia Appendix 1.

Hypothesis 1:

Primary outcome measures: Prolonged abstinence and point prevalence of smoking abstinence.Secondary outcome measures: Seven-day point prevalence of smoking abstinence, mean number of quit attempts since participation in the trial, number of uses of other smoking-cessation services since joining the trial, and number of cigarettes smoked weekly (if still smoking).

Hypothesis 2:

Mediation measures: Importance and self-efficacy of quitting and staying smoke free.

Prolonged abstinence is defined according to the Russell standard definition [38], applying the usual threshold of not smoking more than 5 cigarettes in the past 8 weeks (thus allowing for a 4-week grace period). The 8-week period is then adjusted to 5 and 11 months at 6- and 12-months of follow-up, respectively. Point prevalence of smoking abstinence is defined as not smoking any cigarette in the past 4 weeks, which aims to capture delayed effects of the intervention, as suggested by the Society for Research on Nicotine and Tobacco [39]. Importance and self-efficacy will be investigated by two questions (Multimedia Appendix 1) rated on a scale of 1 to 10.

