For all models, coefficients of interest will be assessed for statistical significance using a null hypothesis testing approach, where tests will be two-tailed at the .05 significance level with 95% CIs. Alongside the null hypothesis tests, posterior distributions using a Bayesian approach will be calculated for each coefficient [41]. Both significance tests and posterior distributions will create a basis for scientific inference.

#### Hypothesis 2

Mediators will be explored using a causal inference framework [42], where Monte Carlo methods are relied upon for inference. This allows for any type of model (linear and nonlinear) to be used to represent the relationships between the group allocation, mediating variable, and the outcome. Three models will be created for each outcome measure, two of which investigate the mediating factors on their own and a third that incorporates both mediators at once. If any baseline characteristics are found to moderate the effect in the primary analysis, additional mediator models will be created to include these characteristics as moderators.

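### The Discussion says the trial is powered for both primary outcomes, but the sample size rests on prolonged abstinence alone; at the protocol's own quoted rates, 4-week point prevalence has about 38% power

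*Protocol article*

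**What the plan says.** The Measures section names two primary outcomes without ranking them: "Primary outcome measures: Prolonged abstinence and point prevalence of smoking abstinence". The second is the stricter one over a shorter window: "Point prevalence of smoking abstinence is defined as not smoking any cigarette in the past 4 weeks". Aims and Hypotheses makes 3 months the primary time point.

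The Power Calculation section has one calculation. It starts from the earlier student trial, in which "25.9% in the intervention group had not smoked more than 5 cigarettes in the past 8 weeks compared to 14.6% in the control group". It summarises this as a Cohen d "value of 0.3, which can be interpreted as a small-to-medium effect", adds that effects of this kind are to be expected from brief digital interventions, and concludes that "we will need to recruit 192 patients per group (at 0.8 power and .05 significance level"). With 10% loss the total is 434. Point prevalence is not mentioned there.

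Previous Research and Findings, in the Introduction, reports the other result of the same student trial: "Differences in the 4-week point prevalence between the groups were also statistically significant (20.6% versus 14.2"%). It also cites two reviews of SMS interventions, with relative increases in quitting of 67% and 63%.

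Under Statistical Analysis, "tests will be two-tailed at the .05 significance level with 95% CIs". The Discussion closes its limitations by saying that "this trial has been designed to power the statistical analyses of two primary outcome measures", and on that ground calls the secondary and mediation analyses preliminary and exploratory.

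**The concern.** The claim of power covers two outcomes, while the effect behind the sample size comes from one. For the other outcome, the protocol quotes a result from the same source trial with the same 4-week window, and the difference is 6.4 percentage points instead of 11.3. A sample just large enough for the larger difference cannot be large enough for the smaller one.

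The stake is how a non-significant point-prevalence result will be read. If the intervention worked as it did among students, that result would occur about six times in ten. A reader who has been told that both primary outcomes were powered could take it for an adequately powered negative, or for a real conflict between the two primary outcomes. The Discussion says that the trial will help decide whether the intervention is offered to all surgical departments in Sweden, so the reading matters.

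**Working it through.** **Inputs.** Two-sided alpha 0.05 (Statistical Analysis). Target power 0.80, 192 per group, 10% loss and 434 in total (Power Calculation). Equal arms, implied by the equal group sizes. Missing outcomes are first handled by complete cases, so about 192-195 per arm are analysable: 434 × 0.9 / 2 = 195. With no loss it is 217.

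**Formula.** For rates p1 and p2, mean p̄ and n per arm:

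power = Φ{ [ |p1 − p2| − 1.96·√(2p̄(1 − p̄)/n) ] / √([p1(1 − p1) + p2(1 − p2)]/n) }

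The arcsine effect is h = 2·asin√p1 − 2·asin√p2, with n per arm = 2(1.96 + 0.8416)²/h².

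**Step 1: the plan's own figure (prolonged abstinence, 25.9% vs 14.6%).**
- h = 0.284, so n = 2 × 7.849 / 0.284² ≈ 195 per arm.
- 195 / 0.9 = 216.7, rounded up to 217 per arm, which is 434 in total. The stated total is reproduced.
- Power at 192: (0.113 − 1.96 × 0.04101) / 0.04061 = 0.803, so 78.9%. At 195: 79.5% (80.0% by arcsine).

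The planned size therefore fits prolonged abstinence. As a side remark, d = 0.3 taken literally gives 175 per arm, and 192 / 0.9 gives 214 per arm (428), so the printed intermediate figures do not quite fit each other. This does not affect the point.

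**Step 2: the same size for 4-week point prevalence (20.6% vs 14.2%).** Here h = 0.169.
- n = 192: (0.064 − 1.96 × 0.03869) / 0.03855 = −0.307, power 37.9%.
- n = 195: (0.064 − 1.96 × 0.03839) / 0.03826 = −0.294, power 38.4%.
- n = 217 (no loss): 42.0%.

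The arcsine method gives 38-39% at 192-195 per arm. At 192 per arm, a simulated chi-square test gives 38% and a simulated unadjusted logistic Wald test 37%. For 80% power, about 550 analysed per arm would be needed.

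**Step 3: the other effects quoted in the protocol, on a 14.2% control rate (an assumption).**

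| Assumed effect | Intervention rate | Power at 192 | Power at 195 |
|---|---|---|---|
| Student trial, point prevalence | 20.6% | 37.9% | 38.4% |
| Review, +63% | 14.2% × 1.63 = 23.1% | 61.5% | 62.1% |
| Review, +67% | 14.2% × 1.67 = 23.7% | 66.3% | 67.0% |

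**Step 4: what 80% would require.** With a 14.2% control rate, solving the formula for the intervention rate gives 25.6% at 192 per arm and 25.5% at 195. That is a difference of about 11.3 points, essentially the prolonged-abstinence effect carried over to the other outcome.

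**The case against.** The best defence is that the Power Calculation does not plan on the student rates as such. It turns them into a standardised effect of 0.3, names no outcome when it adopts that value, and justifies it as typical of brief digital interventions. Read as an arcsine effect of 0.3 for any binary outcome, it gives Φ(0.3 × √(192/2) − 1.96) = Φ(0.979), about 84% power, for point prevalence too. On that reading the Discussion agrees with the stated assumption, and the 38% rests on rates that the protocol never adopted. Those rates come from students aged 21-30, whereas this trial enrols elective-surgery patients of any age who have been told to quit.

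Part of this stands. The protocol cannot be charged with planning on 20.6% versus 14.2%, and 38% should be reported as one scenario. The defence does not rescue the claim, however. The value 0.3 is derived from the prolonged-abstinence rates. On a 14.2% control rate it would imply about 26.1% in the intervention arm, which neither the reported point-prevalence result nor either review effect approaches. The difference in population applies equally to the prolonged-abstinence rates that the protocol does use. Adjustment for baseline covariates may change power modestly but cannot plausibly close a gap from 38% to 80%.

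It is also fair that 95% confidence intervals and posterior distributions are planned, so an imprecise result would be visible to a careful reader. That softens the consequence but does not make the statement correct.

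**Conclusion.** The statement that the trial is powered for two primary outcomes is not supported as written. The design has about 79-80% power for prolonged abstinence. For 4-week point prevalence, power is about 38% at the earlier trial's rates (42% with no loss) and about 61-67% under the cited review effects. These figures assume a two-sided 0.05 test of each outcome, 192-195 analysed per arm and a control rate of 14.2%.

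A reader might infer three stronger things that the documents do not support:
- *That power for point prevalence is 38%, full stop.* It is the figure under one scenario, and the true rates in surgical patients are unknown.
- *That the sample size is wrong.* It is adequate for the outcome on which it was calculated.
- *That prolonged abstinence must become the sole or first-ranked primary outcome.* Ranking is a separate design choice in a registered trial that is already recruiting, and the power figure does not require it.

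The Discussion's description of secondary and mediation analyses as exploratory is unaffected.

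**What to change.** In the Power Calculation section and in the last limitation of the Discussion, state that 434 randomised patients give about 80% power for prolonged abstinence at 3 months only. Beside this, report the expected power for 4-week point prevalence: about 38% at the earlier trial's rates, and about 61-67% under the cited review effects with a 14.2% control rate. Add that a non-significant point-prevalence result is to be interpreted from its confidence interval and posterior distribution, and not as an adequately powered negative.

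The cost is a few sentences and one less favourable stated figure. No extra patients are needed, and no outcome definition or analysis model changes. Whether to order the two primary outcomes is for the sponsor to decide. If it is done, it should be fixed before any results by arm are seen, and it would need a registry update.
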